#### **Anthropometric measures:**

- Body weight:** Weight will be recorded with the participant wearing light clothes and no shoes on the same scale at the baseline clinic visit and at the clinic endpoint (12 months). Additionally, the intervention arm will also self-assess their weight

using the same personal scales at home, at the same time of the day, at baseline and at 2 monthly intervals until and including the endpoint of the study. Participants in the intervention arm will report their weight on the same day their weight has been recorded at home through their two monthly ePRO surveys.

- **Height:** The participant's height will also be measured at baseline in clinic.
- **Body Mass Index (BMI):** This will be calculated using the participant's weight and height and is part of the WCRF/AICR scoring system.
- **Body Composition:** Segmental body composition will be analysed using Bioelectrical Impedence Analysis (BIA) with the Body Composition Monitor (BCM) (Fresenius Medical Care, Bad Homburg, Germany). This is used for an accurate and objective assessment of overall body composition and hydration status (Baumgartner et al, 1988). The BCM device calculates the LBM, lean tissue index (LTI), fat tissue index (FTI), body cell mass (BCM), and adipose tissue mass (ATM), extracellular (ECW), intracellular (ICW) and total body water (TBW) based on measurement values, using physiological modelling and mixture equations (Cole-Cole plot and Hanai formulae and Chamney et al, 2007).
- **Waist circumference:** This measurement will be recorded with the participant not wearing clothing that is directly over the skin. If this is not possible, the measurement may be taken over light clothing. This is also part of the WCRF/AICR standardised scoring system.
- **Muscle strength:** Hand grip strength (HGS) will be measured using the Jamar dynamometer (Jamar Hydraulic Hand Dynamometer, Model 091011725, Sammons Preston Roylean, Nottinghamshire, UK) with its handle in the second position as recommended by the American Society of Hand Therapists (ASHT)(Fess,1986). Grip strength will be measured 3 times per hand, alternating between left and right hand to allow rest and account for any fatigue.
- **Nutritional risk:** Participant's nutritional status will be monitored over the 12 month period on the study database by assessing any change in their Body Composition and MST score.

#### 4.4.6 Survivorship Clinic (complex intervention)

Research and relevant Clinical Staff will be trained in the protocol. Following successful completion of the Ethics Committee approved informed consent process, a unique study identifier will be applied to all subject's study data and will be used exclusively as a unique identifier in study Case Report Forms. Subject's clinical notes will be reviewed, and an appointment arranged at a mutually convenient time to attend the Orchid Centre clinic for the baseline Survivorship clinic visit:

- **For the intervention arm,** the initial Survivorship Clinic visit in the Orchid Centre clinic at CUH will outline a Survivorship Care Plan by the Nurse (Care Plan; see appendix 9a

and 9b), assess and manage current symptomatology and needs per management pathways, refer to appropriate specialists, and ensure future access to the clinic where needed during the 12 month period (see Study Schema Figure 1). Patients in this arm will receive Education and Symptom Management Plan, depending on the outcome of ePRO Symptoms Surveys, or according to clinical judgement (for further information see appendix 14a). The physical nutritional assessments will be undertaken and required Diet Education and Personalised Nutrition Counselling will be performed (For further information see Nutritional Intervention section).

- **For the control arm**, the baseline Survivorship Clinic visit in the Orchid Centre clinic at CUH will outline a Survivorship Care Plan by the Nurse (Care Plan; see appendix 9a and 9b). These patients will follow their usual standard of care outside of the baseline and end of study survivorship clinic visits (see Study Schema Figure 1). The physical nutritional assessments will be undertaken.

At the baseline clinical visit both arms may be advised to use publicly accessible resources currently used in standard clinical care including, but not limited, to the following:

- CUH Exercise Booklet
- ICS Survivorship Booklet or specific Irish Cancer Society Symptom booklets/leaflets
- Irish Cancer Prevention Network Leaflet
- UCC Healthy Eating for Cancer Survivorship
- HSE Let's Get Active leaflet
- Get Ireland Walking Sample Walking Programmes
- HSE Alcohol and Health Leaflet
- Online Websites: ICS, Macmillan.org.uk, Marie Keating, Breast Cancer Ireland, Daisy Network, ARC house etc...
- APPs: Calm, iBreathe, Headspace

At the end of the study, both arms will have an appointment, arranged at a mutually convenient time to attend the Orchid Centre clinic for the end of the study Survivorship clinic visit. The physical nutritional assessment will be reassessed at this point.

### Follow up Assessment and ePRO Trigger System for the intervention group

Patients will complete ePRO questionnaires per Study Calendar depending on which arm of the study they are enrolled in. In addition, patients will self-report weight, and current adjuvant endocrine therapy adherence at each time point.

The Study Team will be aware of severe or worsening ePRO scores and pointed to brief, evidence-based Symptom Management Pathways that outline recommended interventions for managing the relevant symptoms. These evidence-based pathways are based on up to date standard recommendations in oncology clinical guidelines such as those provided by NCCN and ASCO (Study-developed evidence-based pathways for each symptom included in the study are available from appendix 14a to 14n; appendix 14a corresponds to the study pathway structure). We have

pre-defined score thresholds beyond which each symptom will be considered severe enough to trigger an alert. In addition, a worsening of score compared to baseline exceeding a pre-defined threshold will trigger an alert (Further information about study triggers are available in appendix 1b; and information about how a trigger is assessed by the CNMII is available in appendix 14a).

We have selected pre-defined thresholds to identify severe or worsening symptoms based on scores on the ePRO measures and will monitor these thresholds on an ongoing basis. For each ePRO measure, thresholds will be selected to identify severe symptoms or clinically significant worsening of symptoms based on recommended scoring thresholds and prior use of each questionnaire. The selected thresholds to trigger alerts will be reviewed by patient and provider focus groups and will be modified if necessary. Proposed thresholds to trigger an alert for each of the proposed questionnaires are attached as Appendix 1b. Score alerts for PRO-CTCAE measures will be triggered for scores in the severe/very severe categories and for scores that worsen by at least 2 points compared to baseline on a 5 point scale. For the PROMIS measures other than sexual function, score alerts will be triggered for T scores more than 2 standard deviations more severe than the population mean score or by T scores that worsen by more than 0.5 standard deviations compared to baseline. The alert trigger for the PROMIS sexual function scale will be for T scores more than 1.5 times more severe than the population mean or that worsen by more than 0.5 standard deviations compared to baseline. These thresholds were selected based on review of the available literature regarding these questionnaires and are thought to identify severe symptoms and/or clinically significant change in symptoms. Trigger points can be overridden by clinical judgment if required and such action will be documented in the Nurse Record Form.

Since PROMIS T scores cannot be calculated if a patient does not complete all questions in the questionnaire and we do not want to miss clinically significant symptoms of depression or anxiety, an alert will also be triggered in the setting of incomplete depression and anxiety questionnaires if the answer to any key individual question is “often” or “always”.

When addressing the symptoms identified through the ePRO measures, the first step in each recommended clinical pathway is to confirm the presence of the symptom(s). By doing so, we will be able to refine the trigger thresholds and to ensure that the pathways are followed when clinically appropriate. We will record scores that have been triggered and track clinical interventions in response to ePRO score alerts in the patient medical chart and extract the data for analyses by chart review.

Patients will be given at baseline the dates when they will be receiving the surveys. Patients will be reminded twice to complete the surveys as follows:

- 1st reminder: an automatic reminder will be set up if the system does not detect the survey completed in 24h.
- 2nd reminder: a research team member will call the patient if the survey is not completed with 72h.

After a period of 7 days, the survey will be locked, and the patient will no longer be able to answer that survey.

### **Nutrition for the intervention arm**

The nutrition intervention will include a personalised approach to nutrition education for patients in the intervention arm only. Patients will complete a symptom survey at 2 monthly intervals throughout the study. The symptom survey will act as screening tool to identify nutritional risk. Patient specific nutrition counselling will be offered to patients identified at risk.

***Diet Education and Personalised Nutrition Counselling:*** The main goal of the nutritional intervention is to improve the diet quality of each patient using a standardized nutrition assessment, offering evidence-based diet education and developing personalized nutrition goals. Individual goals and targets will be set during the 1st consultation. Dietary counselling involves the prescription of a therapeutic diet that uses regular foods, which can be further modified to provide for individual requirements. The therapeutic diet is adjusted to the individual's usual diet, thereby recognizing personal eating patterns and preferences, which form the basis for individualized dietary counselling. The prescription identifies the type, amount, and frequency of feeding and specifies the caloric/protein level to attain, together with any restrictions and limited or increased individual dietary components. In addition, nutritional advice can be adapted to respond to specific nutrition impact on symptoms (e.g. dysphagia, constipation, diarrhoea, altered taste and temperature sensitivity). Energy and protein requirements will be calculated only for patients that require specific caloric and protein targets to meet their individualised nutritional goals.

During the initial consultation every patient will be educated on diet and lifestyle factors associated with cancer prevention, based on the World Cancer Research Fund's recommendations (WCRF, 2018). After the initial nutrition assessment, dietetic follow up will be individualised. This includes the number of dietetic sessions required for each patient. This will be decided at the dietitian's discretion based on clinical judgement. In the case where the dietetic caseload may exceed the capacity of the survivorship clinic, an acceptance and non-acceptance criteria for the dietetic clinic caseload was developed, and will be used if required (Appendix 3b). These criteria will ensure that patients requiring more intensive and/or specialised dietetic support will be offered appropriate dietetic care.

#### **4.4.8 Duration of the Intervention**

Patients in the intervention group will participate in the intervention for up to 12 months. They will complete surveys during the first 12 months of the study at 2 month intervals. Charts will be reviewed up to 4 weeks after the last survey to document clinician interventions in response to alerts.

#### **4.4.9 Discontinuation of Subjects**

All patients who initiate the study will be included in the overall analysis. All reasons for discontinuation of participation in the trial will be documented clearly in the trial record.

The reasons for discontinuation may include:

- a) At subject's own request.  
*Note: The reason for discontinuation from the study must be documented.*
- b) Death.
- c) Intercurrent illness or condition that would, in the judgment of the principal investigator, affect assessment of clinical status to a significant degree.
- d) Evidence of disease recurrence during study.
- e) Study is terminated for any reason.
- f) Subject withdraws consent for follow-up.
- g) Subject does not complete 2 consecutive ePRO surveys. In that case, the patient will be given the option to continue receiving surveys or to withdraw from the study.

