### 4.3 Complex Intervention

The Women's Cancer Survivorship Clinic (complex intervention) within the HSE South/South West hospital group is a collaboration with the Enhancing Cancer Awareness and Survivorship Programmes (ECASP) at the School of Nursing at University College Cork; regional Cancer Support Services; Irish Cancer Society Services; amongst others.

This multi-disciplinary nurse-led clinic will span the hospital system, community services and international survivorship efforts (Sidney Kimmel Comprehensive Cancer Center at Johns Hopkins, USA). Participation in the study (intervention arm) will include:

1. Informed consent and ePRO enrollment
2. Baseline questionnaire/needs assessment
3. Receipt of Survivorship Plan
4. Education and Symptom Management Plan
5. Dietetic Evaluation
6. Follow up questionnaire/needs assessment

Symptom pathways will be available for common symptoms assessed in the ePRO measures such as joint pain, depression, anxiety, vaginal dryness, dyspareunia, hot flashes, cognitive impairment and fatigue.

Those in the **intervention arm** will undertake ePRO at baseline, 2, 4, 6, 8, 10, 12 months. Triggers to the study team will prompt symptom evaluation and management in between routine clinic visit. A phone call from the clinic nurse will take place @ 6 months also to follow up on progress, symptoms etc.

Those in the **control arm** will undertake ePRO at baseline 12 months. They will have usual follow up care over the 12 month period of the study, after attendance at the Survivorship Clinic. Where participants in the control arm contact the Survivorship team for clinical or other advice, they will be referred to the usual care pathway.

Patient stakeholders/advocates will help to co-design the symptom management resources and the survivorship clinic in partnership with the project team. They will be an integral part of the Steering Committee which will lead the development and conduct of the clinical and research components of the pilot until completion.

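### The two-missed-surveys rule prompts withdrawal before month 12 in the intervention arm only, putting month-12 data at one-sided risk

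*Protocol*

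**What the plan says.** Section 4.4.9 introduces its list in permissive terms: "The reasons for discontinuation may include". Three entries matter here. Reason (c) is an intercurrent illness that, in the principal investigator's judgement, affects assessment. Reason (d) is "Evidence of disease recurrence during study". Reason (g) is "Subject does not complete 2 consecutive ePRO surveys", followed by: "In that case, the patient will be given the option to continue receiving surveys or to withdraw from the study". Withdrawal of consent for follow-up is a separate entry, (f). The same section states: "All patients who initiate the study will be included in the overall analysis".

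Section 4.3 sets the survey schedules. Intervention patients "will undertake ePRO at baseline, 2, 4, 6, 8, 10, 12 months". Control patients "will undertake ePRO at baseline 12 months", which Section 4.4.5 and the calendar in Section 5.2 confirm means baseline and month 12 only.

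Section 4.4.9 does not say whether someone who stops under (c), (d) or (g) is still asked for the month-12 assessment.

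**The concern.** Reason (g) is worded for both arms, but the two schedules make it work differently. A run of two missed surveys can occur in the intervention arm from month 2 onwards. A control patient has only one survey before month 12. She can miss two in a row only by missing both, which is known at month 12, when no follow-up is left to lose.

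The choice offered is also narrow. A patient tired of two-monthly surveys can carry on with them or leave the study. No middle option lets her drop the interim surveys and return at month 12. If she leaves, the month-12 quality-of-life and symptom surveys, the dietary assessment and the body-composition measurement may go with her.

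Sections 2.3 and 3.1 plan to assess the clinic's effect on symptoms and quality of life, the latter section against controls. Section 6.0 intends the between-group estimates to inform a later efficacy trial. Patients who stop answering surveys plausibly differ from the rest in burden or distress. Extra loss of such patients from one arm could bias those estimates, and an analysis model can recover outcomes that were not collected only by assumption.

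Reasons (c) and (d) raise a related but different question. Illness and recurrence are plausibly linked to symptoms and quality of life, so losing month-12 data after them would be outcome-related missingness. They apply equally to both arms, so no imbalance arises from the rule itself.

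**Working it through.** **Inputs from the protocol**

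- Intervention time points: 0, 2, 4, 6, 8, 10 and 12 months, so 7 in all and 6 before month 12 (Section 4.3).
- Control time points: 0 and 12 months, so 2 in all and 1 before month 12 (Sections 4.3, 4.4.5 and 5.2).
- A missed baseline does not stop later surveys in the intervention arm, because dates then run from enrolment (Section 5.1, note a). Baseline therefore counts as a survey that can be missed.
- Planned size: 140 + 60 = 200 patients, which reproduces Section 4.2. No power calculation was made for patient outcomes.

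**Assumptions, because the protocol gives no figures**

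- Each survey is missed with probability q, independently of the others; q = 10%, 20% or 30%.
- A share w of the patients offered withdrawal accept it; w = 0, 0.5 or 1.

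**Step 1: chance of meeting (g) before month 12**

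Let f(n) be the probability of no two consecutive misses in n surveys. Then f(0) = f(1) = 1 and f(n) = (1 − q) f(n − 1) + q(1 − q) f(n − 2). The chance of meeting (g) is 1 − f(n).

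For q = 10%: f(2) = 0.99, f(3) = 0.981, f(4) = 0.972, f(5) = 0.96309, f(6) = 0.95426. So 1 − f(6) = 0.0457.

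| q | Intervention, 6 surveys before month 12 | Control, 1 survey before month 12 |
|---|---|---|
| 10% | 4.6% | 0% |
| 20% | 16.4% | 0% |
| 30% | 32.7% | 0% |

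If baseline is not counted, five surveys remain before month 12 and the intervention figures are 3.7%, 13.5% and 27.3%.

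Over the whole schedule (7 surveys against 2), the chances are 5.4% against 1.0%, 19.3% against 4.0%, and 37.6% against 9.0%. The control figure is q², and it arises only at month 12 itself.

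**Step 2: extra loss of the month-12 assessment**

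A patient who accepts withdrawal adds to the loss only if she would otherwise have completed month 12, which has probability 1 − q. The extra loss is therefore [1 − f(6)] × w × (1 − q). For q = 20% and w = 1: 0.1644 × 1 × 0.8 = 0.132.

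| q | w = 0 | w = 0.5 | w = 1 |
|---|---|---|---|
| 10% | 0 | 2.1 points | 4.1 points |
| 20% | 0 | 6.6 points | 13.2 points |
| 30% | 0 | 11.4 points | 22.9 points |

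The control arm's extra loss from this rule is 0 in every cell.

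Misses that cluster within patients would raise the trigger rate. Those patients would also be less likely to complete month 12 in any case, so the net effect on the extra loss is not determined.

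**The case against.** The strongest reply is that (g) removes nobody. It offers a choice, and any patient may already leave at her own request under (a). The rule adds a prompt and not a new exit, and if every prompted patient continues it has no effect. Section 4.4.6 also provides an automatic reminder and a telephone call, which should keep misses down. The trial is a feasibility study, and survey fatigue in the intervention arm is something it sets out to observe. All of this stands, and it is why the lower end of the extra loss is zero. It does not remove the asymmetry or supply the missing option of staying for month 12 only.

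A reader might infer more than the protocol supports:

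- **That unequal dropout is built in.** It is not. Withdrawal under (g) is optional and the list is permissive. The rule creates a risk whose size depends on what patients choose.
- **That month-12 data are never collected after discontinuation.** Section 4.4.9 is silent. Listing withdrawal of consent for follow-up separately as (f) suggests that other reasons need not end follow-up. Hospital service use over the 12 months is extracted from records (Section 4.4.11), so resource data are not wholly lost either.
- **That this contradicts including all patients in the analysis.** Inclusion is compatible with some missing values.
- **That the primary-endpoint denominator needs changing.** Section 3.3 already uses enrolled patients, so a patient who leaves remains in the denominator.
- **That recurrence causes imbalance.** Reason (d), like (c), applies to both arms, and no recurrence rate is given.

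The word consecutive is not defined. If the quality-of-life and symptom surveys at one visit counted as two consecutive surveys, a control patient could meet (g) at baseline. Counting time points is the natural reading, and the working uses it.

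**Conclusion.** The point holds as a one-sided risk. Applied as written, (g) prompts withdrawal before month 12 in the intervention arm only, and its two options leave out staying in the trial without the interim surveys.

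At assumed independent miss rates of 10%, 20% and 30%, about 5, 16 or 33 of every 100 intervention patients would be prompted, against none of the controls. These figures are chances of being offered a choice. The resulting extra month-12 loss runs from zero to about 4, 13 or 23 points, depending on uptake. The schedules are the protocol's own; the miss rates, uptake and independence are assumptions.

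The exposure lies mainly in the secondary between-arm comparisons of a feasibility trial. For (c) and (d) the point is narrower: the protocol should say whether month-12 outcomes are still sought, because data missing for those reasons would be related to outcome in both arms. The change is worth making because whether data are collected is settled by the protocol and cannot be repaired at analysis.

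**What to change.** Reword (g) so that, after two consecutive missed surveys, a patient may stop the two-monthly surveys and remain in the trial. She is then still sent the month-12 survey and invited to the end-of-study visit. Leaving the study altogether stays available under (a) and (f).

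Add a sentence saying that month-12 outcomes are still sought after discontinuation under (c) or (d) unless consent for follow-up has been withdrawn under (f). State that consecutive refers to survey time points.

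The Drop Out Form needs one line to separate stopping the interim surveys from leaving the trial, so that the two can be reported apart.

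The cost is one protocol paragraph and that form line. The month-12 survey and visit are already scheduled in both arms. The change concerns data collection only and leaves clinical care after illness or recurrence untouched.

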#### 4.4.10 Usability and Satisfaction

In order to gather information on usability and satisfaction with the computerized questionnaire system, the opinions of patients will be gathered using a modified five-item Usability Survey and four item Satisfaction Survey (Lewis, 1995 and Sharma et al, 2016). The questions in this index are designed to assess different domains of usability of the web-based system, including usefulness, ease of use and satisfaction with use, and were adapted from a previously developed computer usability and satisfaction questionnaire. The survey will also include some open-ended questions allowing participants to share their perspectives more freely.

As part of the process evaluation, all patients, health care professionals and the broader team involved in the development and implementation of the clinic will be invited to attend either a focus group or one to one interview that will take place after the completion of their involvement in the study (in person or remotely). Attendees will be asked about their experiences of the survivorship clinic and associated processes, limitations, challenges and possible benefits and future possibilities concerning the intervention. The interview will be audio-recorded with the consent of participants (both patients and HCPs), and will last approximately one hour. Transcribed audio will be analysed using qualitative content analysis. A priori it is anticipated that we will interview up to twenty patients, ten members of the MDT and ten broader team/stakeholders/service providers. A lesser number may be required if data saturation is attained earlier.

